## Methods: participants, interventions, and outcomes

### Study setting {9}

Individual and group-based sessions will take place using online video calls, with all information given via an online platform and a mobile app. Data collection was limited to participants living in The Netherlands, as test tubes for HbA1c assay needed to be sent back to the clinical laboratory in Amsterdam, The Netherlands, in a relatively short period of time. Recruitment of this trial started in July 2024, with the treatment period and first data collection starting in September 2024. The entire study will continue over a period of 3 years.

### Eligibility criteria {10}

Eligible study participants are adults with an indication to be referred to a CLI by their general practitioner (Table 1). In addition, participants are excluded if they (1) are unable to provide written informed consent; (2) have serious mental impairment which would prevent them from understanding the study aim; (3) are pregnant; (4) work night shifts; and/or (5) take sulfonylurea medication. The latter is excluded, as the effects of reducing the eating window (part of the TIMED CLI) on the risk of hypoglycaemia in participants taking sulfonylurea medication is not sufficiently known.

**Table 1 Tab1:** Eligibility criteria for inclusion in the pragmatic trial: Indication for referral to a CLI

• Aged 18 years or older • Either (1) obesity (BMI ≥ 30 kg/m^2^); or (2) overweight (BMI ≥ 25 and < 30 kg/m^2^) with at least one comorbid condition: ◦ Sleep apnoea ◦ Vascular diseases ◦ Type 2 diabetes ◦ Osteoarthritis ◦ Increased waist circumference (men ≥ 102 cm; women ≥ 88 cm) • Motivated to change lifestyle behaviour • Digitally skilled and in the possession of a smartphone • Being able to speak and understand the Dutch language	

*CLI *Combined Lifestyle Intervention, *BMI *body mass index

### Who will take informed consent? {26a}

Informed consent will be obtained via the Electronic Data Capturing software (Castor EDC) [67]. An invite to the electronic informed consent form will be sent by mail after the coordinating researcher talked to the participant to answer any questions and before the start of any study-related assessments.

### Additional consent provisions for collection and use of participant data and biological specimens {26b}

This is not applicable, as no ancillary studies will be performed.

## Interventions

### Explanation for the choice of comparators {6b}

#### Standard CLI

Participants randomized to the standard CLI receive the online CLI (CooL-MiGuide) as it is currently provided as Standard of Care. In short, the programme consists of a basic programme (6–8 months) and a maintenance phase (16–18 months), each including four individual sessions (45 min each) and eight group sessions (90 min each) to help participants change their lifestyle behaviours. All sessions (both individual and group sessions) will be held with the same registered lifestyle coach. Participants can use the MiGuide app and online platform to access more information and to help them adhere to the lifestyle changes. CooL-MiGuide aims to identify individual unhealthy behaviours and pitfalls and provide personalized tools to help change towards healthier behaviours. Consequently, participants may prioritize certain behaviours that are of importance to them. The standard evaluations of MiGuide will provide insight in changes in the quantity of the behaviours throughout the programme and help identify which behaviours they focused on to change. The standard CLI consists of pre-approved topics that are explained in presentations and on the MiGuide platform. All coaches received training by MiGuide in order to provide the CLI in the same way. No alterations are made to this standard CLI. The standard CLI did not include any information about timed lifestyle, and no information was left out. A full overview of the standard CLI can be found in Additional file 1. However, participants have access to external information on timed lifestyle behaviours, such as on social media or news platforms. Coaches in the control arm are instructed to not discuss timing concepts during the CLI sessions, but they are not forbidden to answer questions on timed lifestyle behaviour by participants.

### Intervention description {11a}

#### TIMED CLI

Participants randomized to the TIMED CLI receive the same CLI and can use the app and online platform as described above. In addition, they receive specific education on timing of healthy lifestyle behaviours during the day as depicted in Fig. 2. The education regarding the timing of lifestyle factors is based upon patients’ experiences, systematic reviews of the TIMED consortium [77, 78], and previous observational and experimental research [24, 36, 39, 41–69]. These show that the specific timing of sleep, meal intake, and exercise throughout the day can improve glycaemic and metabolic control. More specifically, the education will consist of the following: (1) sleep 7–8 h per night, with a consistent rhythm on weekdays and weekend days (e.g. between 22.30 and 06.30 h), prevent daytime sleeping and prevent blue light exposure 30 min prior to bedtime; (2) eat within a 12-h eating window (e.g. between 08.00 and 20.00 h), always eat breakfast, and eat the largest part of the daily caloric intake at breakfast or lunch; and (3) schedule exercise in the afternoon or evening (e.g. between 15.00 and 20.00 h). Additional information on the working mechanisms in the human body and practical tips will be explained and repeated in all group and individual sessions, and on the online MiGuide platform.

**Fig. 2 Fig2:**
[figure not shown]
The timed lifestyle advice on sleep, food intake, and exercise for the TIMED GLI

To minimize the risk of contamination between study arms, separate presentations and distinct sections of the MiGuide platform will be used for each intervention condition. Whether participants access the appropriate content (TIMED CLI or standard CLI platform) and receive the correct presentation will be monitored. Prior to the start of each group, the researcher will confirm the correct group allocation with the lifestyle coach. In addition, one of the researchers attends the first group session to provide additional information about the research and verifies that the participants receive the presentation corresponding to the allocated study arm. As mentioned, participants identify their individual unhealthy behaviours and pitfalls, and may therefore focus on personalized selection of behaviour(s). Although all timed recommendations are explained as equally important during the sessions, participants may prioritize certain recommendations based on their personal preferences and problems. Changes in the quantity and the timing of different lifestyle behaviours will be monitored, as described in the Outcomes section.

### Criteria for discontinuing or modifying allocated interventions {11b}

There are no criteria of discontinuing or modifying the allocated intervention. Since the trial is pragmatic, participants receive additional education, and discuss regularly with the assigned lifestyle coach which factors they will work on. This is part of the working mechanisms of the standard CLI.

### Strategies to improve adherence to interventions {11c}

There are several strategies in place to improve adherence to the intervention. First, there will be a presentation for all groups as part of the first group session by the researcher, which participants must attend. In this presentation, information regarding the research will be discussed. Additionally, participants of the TIMED CLI will receive education on the working mechanisms and advice during this presentation, and this education will be reiterated during other group sessions and individual sessions by the lifestyle coach. All information is also available on the MiGuide online platform, which is accessible at all times and will be stimulated by the coaches.

### Relevant concomitant care permitted or prohibited during the trial {11d}

There are no restrictions regarding concomitant care and medication use during this study.

### Provisions for post-trial care {30}

After the trial, participants from both groups will be instructed to keep up their new lifestyle behaviours, including the timed lifestyle behaviours within the TIMED CLI. After 2 years, these behaviours are expected to have been incorporated into the participants’ routine.

### Outcomes {12}

#### Primary outcomes

##### BMI

BMI is selected as the primary outcome of this study, because weight reduction is the main aim of the CLI. Given the pragmatic nature of our study design, we aim to maximize the use of the existing intervention while minimizing the need for additional modifications. As BMI is routinely assessed within the standard evaluations all CLIs, its use aligns with the pragmatic approach and limits additional burden to the participant. In addition, we prioritized BMI over other metabolic outcomes, as BMI represents changes in energy balance, it is most reported in other studies on CLI and/or timing of lifestyle, which enhances comparability of our results, as well as being an easy-to-measure outcome, which would aid implementation of the intervention. Participants measure their bodyweight in the morning with an empty bladder, wearing only their underwear, and their height while barefoot, at baseline, and at 3, 9, and 24 months. BMI will be calculated by dividing bodyweight in kilograms by height in meters squared (kg/m^2^).

### Secondary outcomes

#### Fasting blood glucose and HbA1c

Participants receive the Contour Plus Blue glucose monitor, including test strips, lancing devices, and an information sheet. Using the device, they measure their blood glucose in the morning after an overnight fast (no food and drinks for ≥ 10 h) with a fingertip prick, at baseline, and at 3, and 9 months. The result, together with a photo of the measurement on the device, will have to be entered in the electronic questionnaire sent by email. The Contour Plus Blue glucose monitor was tested in different studies, showing compliance with the International Organization for Standardization accuracy criteria (ISO 15197:2013 [79]) and significantly lowers mean absolute relative differences from the reference value, compared to four other blood glucose monitor systems [80, 81].

HbA1c levels will be estimated using a high-performance liquid chromatography assay, at baseline, and at 3, and 9 months. Participants will collect four drops of blood from a fingertip prick in an HbA1c test tube using the materials and instructions provided. The test tubes will be sent to the Amsterdam UMC – VUmc clinical laboratory to perform the assay, using a medical return envelope, at the day of collection. When temperatures are < 4 or > 25 °C, participants will be asked to drop off the package at a parcel delivery point. This procedure was previously tested and showed feasible and reliable results, with an uncertainty of 3.7% [82].

#### Waist circumference

Participants will receive a measuring tape and instructions to measure their waist circumference in centimetres at the level midway between the lowest rib margin and the iliac crest while standing in a relaxed standing position with the feet approximately 30 cm apart. Waist circumference will be collected at baseline, and at 3, 9, and 24 months.

#### Health-related quality of life

The Dutch form of the PROMIS Scale v1.2 – Global Health will be used to assess mental and physical health. The scale is efficient in the assessment of self-reported health and predictive of health care use [83, 84] and will be taken at baseline, and at 3, and 9 months.

#### Timing of food intake

The timing of food intake will be assessed by the chrono-nutrition questionnaire at baseline, and at 3, and 9 months. The questionnaire consists of eight closed questions on meal regularity, seven closed questions on meal frequency, and 11 closed questions on the timing of meals. The questionnaire was first developed for a study on chrono-nutrition and diet quality in adolescents with delayed sleep-wake phase disorder [85]. Questions are based on questionnaires and literature from other studies about the relationships between chrono-nutrition, metabolic syndrome, and the biological clock [85]. This specific timing of eating questionnaire has not been validated; however, similar chrono-nutrition questionnaires show great validity [86].

#### Timing of sleep

A questionnaire consisting of 14 items on sleep duration, insomnia, shiftwork, daytime napping, and use of sleep medication will be taken at baseline, and at 3, and 9 months. The questionnaire is a combination of (parts of) the validated Munich Questionnaire and the validated Epworth Sleepiness Scale [87–89].

#### Timing of physical activity

No golden standard regarding questions on timing of physical activity exists. Thus, separate questions will be asked regarding the timing of physical activity at baseline, and at 3, and 9 months.

#### Acceptability of the intervention

To measure the acceptability of the intervention, the generic form of the validated theoretical framework of acceptability questionnaire [90] will be used, which was translated to Dutch. Subdomains of the acceptability questionnaire will be used to evaluate the affective attitude, perceived burden, perceived effectiveness, and self-efficacy regarding the intervention. This questionnaire will be taken at baseline, and at 3, and 9 months.

#### General questionnaires

The general questionnaires used in the MiGuide evaluation include questions on education level, employment status, alcohol consumption, smoking behaviour, physical activity, and dietary intake through a food diary. This questionnaire will be taken at baseline, and at 3, 9, and 24 months.

#### Participant timeline {13}

Participants will be informed about the study through a participant information folder and informed consent form. Participants will be asked to provide consent for the use of their data gathered via the MiGuide app and platform, as well as through the evaluation forms used by MiGuide.

To evaluate the effects of the interventions, the above-mentioned outcomes will be measured at different times during the study (see Table 2 for an overview of measurements). A part of this data is routinely collected as part of standard care; however, some additional measurements are included specifically for this study. All measurements and questionnaires are asked in participants in the standard CLI and TIMED CLI.

**Table 2 Tab2:**
[figure not shown]
Schedule of enrolment, interventions, and assessments of the pragmatic trial

*BMI *body mass index, *PA *physical activity, *EQ-5D-5L *Euro-Quality of Life 5-dimensional questionnaire, *T2D *type 2 diabetes, *HR-QoL *health-related quality of life, *TFA *theoretical framework of acceptability

### Sample size {14}

To our knowledge, no previous study has compared effects of education on timing of a combination of different lifestyle behaviours, with routine care CLI on any outcome. We could thus not use such studies to inform our power calculation. Therefore, we based our sample size calculation on our primary outcome of BMI based on a study comparing caloric restriction with and without time-restricted eating in participants with obesity [91]. This study by Liu et al. [91] found a 0.7 kg/m^2^ greater reduction in BMI in time-restricted eating after 12 months compared to caloric restriction alone. Although cluster randomization will be used, we expect minimal within-cluster correlation, since the clustering is solely on participants’ personal schedules rather than shared characteristics such as place of residence. To further minimize potential correlation, groups will be scheduled on different days and at different times of day. To detect a difference of 0.7 ± 0.9 kg/m^2^ in BMI with an *α* of 0.05, and *β* of 0.1, an intraclass correlation coefficient of 0.02, and a cluster size of 8–12 participants, we calculated that 45 participants per group are required. Accounting for 10% attrition rate, a total of 50 participants per group will be enrolled.

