## Assignment of interventions: allocation

### Sequence generation {16a}

A minimum of ten groups will be scheduled for the pragmatic trial. These groups will be cluster-randomized (1:1) to either the TIMED CLI or the standard CLI using a randomization list (block size of 4) made by an independent statistician using *Randomizr* packages (version 1.0.0) in RStudio (version 4.4.0).

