## Statistical methods

### Statistical methods for primary and secondary outcomes {20a}

Baseline characteristics will be described by intervention arm as mean ± standard deviation, median and interquartile range (if not normally distributed), or numbers and percentages if categorical. Statistical analyses will be performed using RStudio. An intention-to-treat analysis will be performed for both primary and secondary outcomes using multiple linear mixed models to compare changes between baseline, and at 3, and 9 months and compare between intervention arms. For BMI and waist circumference, effects will also be estimated at 24 months. The models will account for clustering within CLI groups, and outcomes that are not normally distributed will be log-transformed prior to analysis.

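### The 90% power claim makes no visible allowance for having as few as ten randomised groups (about 85% at the protocol's own ICC), and the reason given for a low ICC is incomplete

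*Protocol article*

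**What the plan says.** The section Sample size {14} sets the target as follows: "To detect a difference of 0.7 ± 0.9 kg/m^2^ in BMI", "with an *α* of 0.05, and *β* of 0.1", and then "an intraclass correlation coefficient of 0.02, and a cluster size of 8–12 participants, we calculated that 45 participants per group are required". Attrition is added next: "Accounting for 10% attrition rate, a total of 50 participants per group will be enrolled". The section does not give the number of groups used in the calculation, name the formula, or cite a source for the ICC.

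The number of groups is given elsewhere. Sequence generation {16a} says "A minimum of ten groups will be scheduled for the pragmatic trial", and Trial design {8} gives the same minimum with 1:1 allocation.

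The low ICC is justified by the claim that groups are formed only on participants' personal schedules. The section adds: "To further minimize potential correlation, groups will be scheduled on different days and at different times of day". The description of the standard CLI says "All sessions (both individual and group sessions) will be held with the same registered lifestyle coach". It also sets eight group sessions in each of two phases, 16 in all. The TIMED arm receives the same programme with the timing education added.

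For the analysis, Statistical methods {20a} plans linear mixed models of change from baseline and says "The models will account for clustering within CLI groups".

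**The concern.** When groups are randomised, the arm effect is judged against variation between groups. With five groups per arm that variation is estimated on 8 degrees of freedom, so the two-sided 5% critical value is 2.31 rather than 1.96. A design effect inflates the variance but leaves the critical value unchanged, so with few groups it overstates power.

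The ICC argument matters because power falls quickly as the ICC rises above 0.02. Being formed by schedule describes how people enter a group. It says nothing about the correlation that builds up afterwards, when the same people share a coach and group sessions for two years. If the power is overstated, a null result will be read against a sensitivity that the trial did not have.

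**Working it through.** **Inputs.** From Sample size {14}: difference 0.7, SD 0.9, α 0.05 (taken as two-sided), β 0.1, ICC 0.02, group size 8–12, 45 per arm analysed and 50 enrolled. From Sequence generation {16a} and Trial design {8}: at least ten groups, 1:1, taken as five per arm.

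**Reproducing the stated 45.**
- Individually randomised n per arm = 2 × (1.960 + 1.282)² × (0.9/0.7)² = 34.7, rounded up to 35. An individual-level t-test needs 36.
- Design effect = 1 + (m − 1) × 0.02, which is 1.14 at m = 8 and 1.22 at m = 12.
- Product: 34.7 × 1.14 = 39.6 to 34.7 × 1.22 = 42.4. With the t-test, 36 × 1.22 = 43.9, rounded up to 44.
- A one-sided α gives 29 before inflation and 29 × 1.22 = 35.4, rounded up to 36, which does not fit.
- Attrition: 45/0.9 = 50, as stated.

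The stated 45 is therefore close to the upper end of a large-sample design-effect calculation, but not exactly equal to it. On that formula 45 per arm has 91.6% (m = 12) to 93.3% (m = 8) power.

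**Allowing for the number of groups.** With k groups per arm, m = n/k analysed per group and df = 2(k − 1):
- SE = 0.9 × √(2 × DE/n), where DE = 1 + (m − 1) × ICC
- noncentrality = 0.7/SE, and power is taken from the noncentral t distribution on df.

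For k = 5, n = 45, m = 9, ICC 0.02: DE = 1.16, SE = 0.2044, noncentrality = 3.425, critical value 2.306 on 8 df. Power = 85.0%. A simulation of the group-level t-test (200,000 runs) also gave 85.0%.

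| Groups per arm | Analysed per arm | ICC | Power, t on 2(k − 1) df | Power, normal |
|---|---|---|---|---|
| 5 | 45 | 0 | 89.6% | 95.8% |
| 5 | 45 | 0.02 | 85.0% | 92.9% |
| 5 | 50 | 0.02 | 87.9% | 94.7% |
| 6 | 45 | 0.02 | 87.8% | 93.5% |
| 7 | 45 | 0.02 | 89.5% | 93.9% |
| 6 | 50 | 0.02 | 90.4% | 95.3% |
| 5 | 45 | 0.05 (assumed) | 77.9% | 87.7% |
| 5 | 45 | 0.10 (assumed) | 67.4% | 78.5% |

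Ten groups randomised in blocks of 4 need not split 5:5. A 6:4 split with 9 analysed per group gives 83.5% at ICC 0.02. To reach 90% at ICC 0.02, five groups per arm need 11 analysed in each (55 per arm, 90.2%). Six groups of 9 per arm (54 per arm) give 92.1%.

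**The ICC rationale.** The sample size section treats schedule as the only source of clustering. The intervention description names two more: a common coach and 16 common group sessions. Placing groups on different days and times does not make members of one group less alike, so it cannot be expected to lower the correlation. Because people are assigned by preferred slot, it may make groups differ more.

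**The case against.** Several points on the other side stand.

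- **Ten groups is a floor.** Groups of 8 would mean more than five per arm, and the realised number is not in the document. With six groups per arm and 50 analysed, the stated 90% is met. The shortfall at ICC 0.02 is therefore between about 0 and 5 points for equal allocation, and 85% should not be read as what the trial certainly has.
- **The formula is inferred.** The document does not name it, and the reconstruction reaches 42.4 or 44 rather than 45. The small excess offsets part of the loss.
- **The calculation is for one between-arm comparison, while the planned model is longitudinal.** With only a random group intercept and balanced data, the group effect cancels from the arm-by-time contrast, and software would assign it far more than 8 df. Baseline adjustment or repeated measures could also change the power. The sample size section, however, claims no gain from either. A model in which group effects cannot change over time also leaves out the clustering that a shared coach and sessions would produce in BMI change.

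Three stronger readings are tempting and not supported. A reader might infer that the scheduling argument is exactly reversed and that the ICC must exceed 0.02. That slot choice sorts people in ways related to BMI change is plausible, but no data in the document show it, and night-shift workers are excluded. A reader might take 78% or 67% as the trial's power, but those figures rest on assumed ICCs. A reader might also infer that the primary test will exceed its 5% error rate. The document does not specify a Wald z test, a simulation of that test at ICC 0.02 gave only 5.3%, and the choice of degrees of freedom is commonly left to the analysis plan.

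**Conclusion.** The stated power is not supported by the protocol's own inputs at the minimum number of groups. With ten equal groups and 45 analysed per arm, a group-level comparison at ICC 0.02 has about 85% power, a type II error near 15% rather than 10%. Even an ICC of zero gives just under 90%. More groups or less attrition narrow the gap, and some combinations close it.

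This rests on a two-sided 5% test, equal group sizes, a 5:5 split and a single between-arm contrast on group-level degrees of freedom. Separately, the case for a low ICC is incomplete: it overlooks the shared coach and sessions, and the scheduling argument gives no reason to expect lower correlation. The value 0.02 therefore has no stated support, and power is sensitive to it.

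**What to change.** 1. In Sample size {14}, restate the power for the realised number and sizes of groups, using a t-based calculation at ICC 0.02 and over a range of larger values labelled as assumptions. Recruitment closed in July 2025, so the number of groups should now be known to the sponsor.
2. Delete the claim that scheduling on different days and times reduces correlation. Acknowledge that a shared coach and shared sessions can create it.
3. For the arm-by-time contrasts, specify a model that lets group effects vary over time, or a baseline-adjusted model with a group random effect. Use Satterthwaite or Kenward-Roger degrees of freedom. A group intercept alone with either method would not necessarily bring in the group-level degrees of freedom. If the analysis plan already does this, a cross-reference is enough.

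**Cost.** This is a change of wording and a model specification, with no extra participants. The stated power becomes somewhat less favourable and confidence intervals somewhat wider. With ten groups the multiplier is 2.306 instead of 1.960, about 18% wider for the same standard error (2.306/1.960 = 1.18).
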